### Central hemodynamics, sympathetic inhibition and hypertension

The CBP has a predictive value in the risk stratification of cardiovascular morbidity and mortality as demonstrated by the CAFE (Conduit Artery Function Evaluation) study. This study showed different effects on the CBP of groups treated with amlodipine and atenolol even though reductions in peripheral arterial pressure were similar. This difference has been suggested to be responsible for the favorable cardiovascular outcomes in the amlodipine group of the ASCOT study (Anglo-Scandinavian Cardiac Outcomes Trial), which demonstrated the importance of CBP control in relation to peripheral BP and how it can be influenced by certain drug therapies [38].

The CBP is directly influenced by arterial stiffness; the arteries, especially the aorta and carotid, are estimated to stiffen by about 10 to 15 % in men and 5 to 10 % in women each decade [39]. Arterial stiffness is a major determinant for the increase in the pulse pressure (PP) and CBP, variables considered risk predictors of myocardial infarction, stroke, and heart failure. In addition, higher cardiovascular morbidity and mortality have been associated with increased CBP, especially in hypertensive diabetics, the elderly, and chronic renal disease patients [40, 41]. Thus, advanced age and high BP are the two most important variables for increased arterial thickness and, consequently, arterial stiffness.

The influence of arterial stiffness on the CBP explains why the pulse wave, generated in every left ventricular ejection period, propagates cyclically throughout the arterial tree to the peripheral arteries. Changes in the impedance and structural or geometric discontinuity of the arterial tree along its path generate reflected waves that move backwards into the ascending aorta and to the heart (backward wave). Therefore, the CBP is the sum of the anterograde and retrograde (reflected wave) components [42, 43]. Wave propagation is amplified from the central aorta to the peripheral arteries. That is, the amplitude of the pressure wave will be greater in peripheral arteries than in the central arteries, which explains the increased pressure in the brachial artery compared to the aorta (central) in younger individuals (the CBP is about 10 to 20 mmHg lower than the peripheral BP). With aging, a loss occurs in arterial elasticity, increasing both the arterial stiffness and the PWV. Increased PWV causes a faster return of the reflected pulse wave with early overlap of the reflected wave during systole (unlike what happens in healthy young people when the reflected wave returns later in systole). This leads to an increase in the systolic pressure and elevation in central PP (PP amplification), which, in turn, increases the afterload on the left ventricle and reflects an increase in the CBP, which almost equals the peripheral BP [43, 44]. This increase in the CBP caused by the reflection of waves is known as the augmentation index (AIx). Hence, the AIx is an alternative index derived from the analysis of the central aortic pressure curve and quantifies the effect of reflected waves [45–47]. It has the advantage of taking into account the time of anterograde and retrograde waves, which are the main determinants of CBP.

Currently, nonpharmacological therapeutic methods are being used to treat RH. These are invasive, require long-term follow up to monitor the results and may cause unwanted complications during and after the procedure, besides being expensive. Examples of these methods are denervation or ablation of the renal sympathetic ganglia and chronic carotid baroreflex stimulation [48]. Both these techniques have generated good results in the reduction of peripheral BP by improving vasomotor tone related to sympathetic suppression; however, similar reductions in BP were reported for treatment and placebo groups [48, 49]. Thus, the identification of new noninvasive therapeutic approaches to control RH is essential. Transcutaneous electrical nerve stimulation (TENS) may be a new, easy to apply, reproducible, and inexpensive technique for this purpose. TENS is capable of inhibiting primary afferent pathways using low-frequency electrical pulses generated by electrodes attached to the skin, which cause local numbness and thus inhibit pain [50, 51]. In addition to the analgesic effects, electrical stimulation has been shown to enhance a local vasodilator effect, which may contribute to reducing BP and prevent ischemia [52]. Among the mechanisms that might explain this anti-ischemic action are the inhibition of sympathetic segmental vasoconstriction, release of vasodilatory peptides from sensory neurons, and the pump effect of muscle contractions [53–56]. Other favorable effects have been observed on applying TENS in the cervicothoracic ganglion region. The cervicothoracic ganglion or stellate ganglion, whose predominant action is sympathetic activity, is a confluence of nerves located in the posterior cervical region at the junction of the lower and upper thoracic cervical ganglia [53–58].

Mannheimer et al. demonstrated that low-frequency electrical stimulation applied to the suprathoracic lymph node region produced an anti-ischemic effect by reducing myocardial oxygen demand due to the reduction in the afterload resulting from a reduction in BP [53]. This response, which is hypothetically based on the observed reduction in epinephrine and norepinephrine levels, may involve a reduction in sympathetic nervous system activation [53, 57]. In turn, Silva et al. observed that TENS applied to the suprathoracic ganglion region during exercise might be associated with decreased peripheral and central BP in healthy young people, a response indicated by significant changes in heart rate variability [58].

Given the scarcity of publications in the scientific literature, this innovative work will study the effects of the application of TENS in the suprathoracic lymph node region to reduce peripheral BP and CBP in RH patients.

### Rationale

Due to the high incidence of cardiovascular morbidity and mortality caused by RH, the introduction of new, more effective, highly specific, and noninvasive therapeutic approaches that are reproducible and less costly from a financial point of view are needed.

### Research question

The following research questions will be explored:Does TENS constitute a new therapeutic option in the reduction of peripheral blood pressure of patients with resistant hypertension?Does TENS constitute a new therapeutic option in the reduction of central pressure of resistant hypertensive patients?Does TENS reduce arterial stiffness measurement parameters?Can TENS positively influence metabolic disorders that involve the progression of arterial stiffness?

### Objectives

The research objectives of this study are as follows:To evaluate the effectiveness of TENS as antihypertensive therapy in RH patientsTo assess the peripheral and central BP before and after the use of TENSTo evaluate the behavior of arterial stiffness by measuring the AIx and PWV before and after the use of TENSTo observe the biochemical changes, inflammatory markers, and the participation of RAS inhibitors before and after the application of TENS

## Methods/design

### Design

The present trial (clinicaltrials.gov identifier: NCT02365974, registered on 8 February 2015) will be a randomized, open-label, parallel-assignment study controlled with a sham group. All patients who participate in the research will sign informed consent forms. The project design, approved by the Research Ethics Committee of FAMERP, São Paulo, Brazil, which is accredited by the Office of Human Research Protections as an Institutional Review Board (CAAE n° 07606212.5.0000.5415, n° 94.248/2012) (Additional file 1), will comply with the following described criteria.

### Inclusion criteria

The inclusion criteria are as follows:RH patients taking at least three antihypertensive drugs at full doses, one of which is preferably a thiazide diureticAge between 40 and 70 years

### Exclusion criteria

The exclusion criteria are as follows:Use of a cardiac pacemakerCardiac electrical conduction abnormalities evidenced by ECG or stress test (ergometry)Dermatological abnormalities at the site of the application of TENSUncontrolled diabetes in patients using oral hypoglycemic agents or insulin with glycated Hb ≥ 7.5 %Secondary hypertensionPatients who do not adhere to the lifestyle changes recommended by their physician such as low-sodium diet and weight lossModerate to severe cervical-thoracic scoliosisObesity with body mass index (BMI) ≥ 35 kg/m^2^

### Random allocation

A computer-validated software program (Random Allocation) will be used for the random allocation. The study coordinator will organize and number the envelopes, which will be allocated in order of patient enrollment. The professional responsible for the Endo-PAT procedure and evaluation of arterial stiffness parameters will be blinded.

### Interventions

TENS will be applied in the cervicothoracic ganglion region in the active comparator group, and the sham group will not be submitted to transcutaneous electrical stimulation. Figure 1 shows a flowchart of the selection of participants and interventions.

**Fig. 1 Fig1:**
[figure not shown]
Flowchart of study

### Randomization and follow‐up

#### Protocol

Patients will be divided into two groups: treatment and control (sham group). The sham group will be submitted to the procedure to fit the stimulation equipment. However, these patients will not be submitted to stimulation. Both groups will undergo a physical examination at the start and end of the study period to determine anthropometric variables. The BMI, defined as the weight (kg) divided by the patient’s height squared (m^2^), will be calculated. The height will be determined in centimeters using a measuring tape while the individual stands in bare feet. Individuals with a BMI < 25 kg/m^2^ will be classified as normal, overweight as a BMI between 25 and 30 kg/m^2^, and obese as a BMI ≥ 30 kg/m^2^. The waist circumference will be measured using a measuring tape at half the distance between the iliac crest and the lower costal margin. Patients will undergo the following tests before and after the end of the 4-week study period: 24-h ambulatory blood pressure monitoring (ABPM), 24-h dynamic electrocardiography, continuous measurement of beat-to-beat BP, endothelial function measurement (Endo-PAT 2000), and radial artery applanation tonometry (AT). Table 1 shows a summary of the key practical aspects of the study with all follow-up visits and requested exams, and Fig. 1 represents the flowchart of the study.

**Table 1 Tab1:** Key practical aspects of the study with all the clinical visits and the requested exams

Visits	Screening	1^st^ week	2^nd^ week	3^rd^ week	4^th^ week
Weeks	−1	1	2	3	4
Informed consent	X				
Inclusion and exclusion criteria	X	X			
Medical history	X				
Medical evaluation/physical examination (BP measure)	X	X	X	X	X
Randomization		X			
Application of TENS (3x/week)		X	X	X	X
Creatinine	X				X
Fasting glucose	X				X
Glycated hemoglobin	X				X
Potassium	X				X
Uric acid	X				X
Insulin	X				X
Total cholesterol	X				X
HDL-c	X				X
Triglycerides	X				X
Urinary sodium	X				X
Urinary potassium	X				X
Microalbuminuria	X				X
GFR estimation	X				X
Specific biochemistry tests		X			X
Ambulatory blood pressure monitoring		X			X
24-h electrocardiographic monitoring		X			X
Evaluation of sympathetic activity		X			X
Evaluation of endothelial function		X			X
Evaluation of arterial stiffness		X			X

*BP* Blood pressure, *TENS* transcutaneous electrical nerve stimulation, *HDL-c* high-density lipoprotein cholesterol, *GFR* glomerular filtration rate

### Ambulatory blood pressure monitoring

ABPM will be performed using the Mobil-O-Graph monitoring device (I.E.M. Gmb, Stolberg, Germany) [59]. Monitoring requires patients to maintain their normal daily activities with the BP being measured automatically at 30-minute intervals for an entire 24-h period according to the technical norms of the 5^th^ Guidelines on Ambulatory Blood Pressure Monitoring [60]. The following parameters will be measured and evaluated over 24 h: systolic (SBP) and diastolic BP (DBP), PP, central systolic and diastolic aortic pressure, central PP, AIx, PWV, cardiac output, and peripheral vascular resistance.

The SBP and DBP will be obtained by ABPM with the mean values for the 24-h period, daytime, and nighttime being considered for analysis. RH patients with mean BP values of ≥ 130 × 80 mmHg over 24 h, ≥ 135 × 85 mmHg during wakefulness, and ≥ 120 × 70 mmHg when asleep will be considered. PP will be calculated during the periods (24 h, daytime, and night) using the formula PP = SBP - DBP. The normal nocturnal dip will be defined as a drop >10 % in SBP from wakefulness to the period of sleeping.

### 24-hour electrocardiographic monitoring

The assessment of the effects of the inhibition of sympathetic nerve activity on the cardiovascular system will be by 24-h dynamic electrocardiography (Holter System - Cardios-Light/Cardios) in accordance with the Guidelines for the Evaluation and Treatment of Patients with Cardiac Arrhythmias [61]. The Holter System will be attached to the patient early in the morning to perform a continuous recording of ambulatory electrocardiographic signals over 24 h. The electrode attachment sites will be shaved and cleaned to reduce skin impedance. During the monitoring period, the patients should continue their normal daily activities. All data will be recorded on a digital recorder, with subsequent analysis being carried out by trained professionals. Recordings will be made using three bipolar precordial leads; the CM5 lead is very sensitive in the diagnosis of changes in heart rhythm and for detecting myocardial ischemia [61, 62].

### Evaluation of sympathetic activity (continuous measurement of beat-to-beat blood pressure)

The continuous measurement system of beat-to-beat BP (NEW Finapres® - Finapres Medical System/Medical Biolink) will be used to evaluate the sympathetic activity. Patients will be placed in a quiet room with controlled temperature (22 °C), without having ingested any kind of natural or drug stimulant and without pain or a full bladder [63, 64]. Before the examination, the patient must remain seated and at rest for 15 min. After placement of the cuffs, the arms will be fully supported at the xiphoid process, and the BP will be recorded for 5 min.

### Evaluation of endothelial function

The peripheral endothelial function will be assessed noninvasively by measuring the reactive hyperemia of the vessel using the Endo-PAT system (peripheral arterial tonometry - Endo-PAT 2000; Itamar Medical, Caesarea, Israel) [65]. Patients will be instructed to appear for this exam after 12-h overnight fasting, including from any kind of medicine. The temperature of the examination room will be maintained between 21 °C and 24 °C, and tight clothing, watches, bracelets, and rings that might interfere with blood flow to the arms will be removed. During at least 15 min, the patients will remain sitting or lying in the examination room to ensure a relaxed cardiovascular status [65–67].

A pressure cuff is placed on one arm (study arm), whereas the other serves as a control (control arm). The device, comprising a pneumatic plethysmograph, is placed on the tip of each index finger, and a uniform pressure is applied to the distal digital surface allowing the measurement of changes in the pulse volume. The insufflation pressure of the digital device is electronically set at 10 mmHg below the DAP or at 70 mmHg. After a 10-min regulation period, the BP cuff is inflated to 60 mmHg above systolic pressure or to 200 mmHg for 5 min. The device continues to record for 10 min after the cuff is deflated. The absence of residual pulsatility is monitored in the occlusion period. The hyperemia after the period of occlusion stimulates endothelium-dependent vasodilation, causing an increase in the amplitude of the digital pulse. Changes in the pressure signals are filtered, amplified, recorded electronically, and analyzed using an automated computerized algorithm (Itamar Medical). The change from the baseline measurement is defined as the reactive hyperemia index (RHI), which will reflect, in part, the vasodilator function of the digital microcirculation. Endothelial dysfunction is defined as a mean value of 2.34 ± 0.33 less two standard deviations of 20 asymptomatic, healthy control subjects with no history of cardiovascular disease and without major risk factors (RHI ≤ 1.68) [67].

### Evaluation of arterial stiffness

The arterial stiffness will also be evaluated by AT of the radial artery, as suggested by taking an average of three measurements after the pressure is stabilized. The HEM9000 AI device (OMRON Healthcare, Co. Kyoto, Japan) will be used for this exam.

The AT examination will be performed in a quiet controlled environment (temperature between 21 °C and 24 °C) after the patient has rested for at least 5 min while sitting with the legs uncrossed, the bladder empty, and away from acute stressors. The patient will not have smoked at all for at least 30 min or ingested alcohol. The OMROM AT equipment uses a radial ultrasonic transducer and cuffs with the correct size for the arm circumference, as recommended by the guidelines to evaluate BP [1].

### Application of TENS

TENS will be applied in the cervicothoracic ganglion region located between the C7 and T4 vertebral processes for 40 min three times weekly for a total of 4 weeks.

Electrostimulators (Endomed 684, Enraf Noniuns, Rotterdam, Netherlands) with two 80-Hz output channels at a pulse width of 150 μs will be used for the application of TENS. The intensity in milliamps (mA) will be adjusted depending on the sensitivity of each individual patient. This electrical stimulus has a high-frequency current that will cause mild local paresthesia without causing pain or unpleasant sensations. The intensity will be increased from zero until the perceived sensation reaches the maximum sensory threshold without pain or discomfort or involuntary muscle contractions. The 5 × 5-cm self-adhesive electrodes (Valutrode mark) are attached to the patient after marking the correct location using a dermatographic pencil and cleaning the skin. The arrangement thereof will be parallel on each side of the C7 (channel 1) and T4 (channel 2) vertebral spinous processes (Fig. 2) [58].

**Fig. 2 Fig2:**
[figure not shown]
Diagram showing the location for application of the transcutaneous electrical nerve stimulation (TENS)

### General biochemistry assessment

Biochemical tests will be performed at two time points, before and after the 4-week study period, and include blood sugar, glycated hemoglobin, total cholesterol (TC), high-density lipoprotein cholesterol (HDL-C), triglycerides (TG), creatinine, potassium, uric acid, and plasma insulin levels.

Blood sugar, TC, HDL-C, and TG levels will be determined by colorimetry after fasting for 12 h using a RXL Dimension device with the Dade Behring reagent. Diagnosis of diabetes mellitus (DM) will be established by patient history, the use of hypoglycemic drugs, and measurement of the serum glucose [68]. The LDL-C fraction will be calculated using the formula LDL-C = TC - HDL-C - TG/5 (for TG < 400 mg/dL) [69]. Additionally, the electrochemiluminescence method will be used to measure plasma insulin (immunoassay for the in vitro quantitative determination of human insulin in serum and plasma using the Elecsys 1010/2010 immunoassay and E170 modular analytics analyzers by Roche). The homeostasis model assessment of insulin resistance (HOMA-IR) index will be applied after obtaining blood sugar and insulin levels in order to determine insulin resistance and the functional capability of the pancreatic beta cells. Insulin resistance will be characterized when this ratio exceeds 2.71 [70]. The HOMA-IR index is calculated using the following formula:$$ \mathrm{HOMA}\hbox{-} \mathrm{I}\mathrm{R}:\;\frac{\mathrm{Fasting}\;\mathrm{insulin}\left(\mathrm{M}\mathrm{c}\mathrm{U}/\mathrm{mL}\right)\times \mathrm{fasting}\;\mathrm{glucose}\left(\mathrm{mmol}/\mathrm{L}*\right)}{22.5}. $$

In order to convert the glucose concentration to mmol/L it is necessary to multiply the value in mg/dL by 0.0555.

Measurement of serum creatinine will be performed by a standardized enzyme-kinetic biochemical test and will be considered high when serum creatinine is > 1.4 mg/dL [71, 72].

Urinary sodium and potassium levels (mEq/L) will be evaluated by flame photometry. Urinary sodium and potassium levels excretion will be calculated by multiplying the urinary sodium and potassium concentrations in mEq/L by the 12-h urine volume [73]. Microalbuminuria will also be evaluated. To evaluate microalbuminuria, the urinary albumin-to-creatinine ratio (UACR) will be obtained from urine samples collected in the morning. Urine creatinine will be calculated using a colorimetric method, and albuminuria will be determined using the nephelometric method. The glomerular filtration ratio (GFR) will be estimated using the modification of diet in renal disease (MDRD) formula: GFR_MDRD_ (mL/min/1.73 m^2^) = 186 (serum creatinine)^−1.154^ × (age)^−0.203^ × (0.742 if female) × (1.212 if black) [74].

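### HOMA-IR and its 2.71 cut-off are not restricted to participants who do not inject insulin, and the index is said to give beta-cell function that its formula cannot give (minor; metabolic question only)

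*Protocol article*

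**What the plan says.** All of this is in the protocol article.

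- **General biochemistry assessment, timing.** "Biochemical tests will be performed at two time points, before and after the 4-week study period". Plasma insulin is measured with an "immunoassay for the in vitro quantitative determination of human insulin in serum and plasma".
- **Same section, use of the index.** The HOMA-IR "index will be applied after obtaining blood sugar and insulin levels", and its purpose is "in order to determine insulin resistance and the functional capability of the pancreatic beta cells". No subgroup is exempted.
- **Same section, formula and threshold.** "The HOMA-IR index is calculated using the following formula": fasting insulin in mcU/mL times fasting glucose in mmol/L, divided by 22.5. Then: "Insulin resistance will be characterized when this ratio exceeds 2.71". No second formula and no beta-cell threshold appear.
- **Exclusion criteria.** Diabetics on oral agents or insulin are excluded when glycated Hb is 7.5 % or higher. Those on insulin with a lower value remain eligible.
- **Table 1.** Insulin and fasting glucose are scheduled for screening and week 4, again without exemption. C-peptide is not among the listed tests.
- **Research question.** The index bears on the fourth question: "Can TENS positively influence metabolic disorders that involve the progression of arterial stiffness"?

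**The concern.** Two features of the stated rule do not fit the population or the formula.

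First, HOMA-IR reads insulin resistance from the insulin the patient secretes in the fasting state. In a patient who injects insulin, the assay result also depends on the product, the dose, the time since injection and whether the assay detects that product. The protocol admits such patients and then applies the index and its cut-off without separating them. A change between screening and week 4 in one of these patients could reflect the injection and not a metabolic effect of TENS.

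Second, the index is given two purposes but has one formula, and that formula serves only the first. A statement about beta-cell function based on it would have no support.

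At stake is the insulin-resistance part of the metabolic research question and of the objective on biochemical changes.

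**Working it through.** **Inputs from the protocol article:** HOMA-IR = insulin × glucose / 22.5; cut-off 2.71; conversion "multiply the value in mg/dL by 0.0555"; eligibility of insulin users with glycated Hb below 7.5 %; 28 per group (Sample size calculation), used below only as a denominator.

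**Assumed, not in the documents:** all glucose and insulin values, and the share of insulin users.

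**1. The plan's conversion.** 100 mg/dL × 0.0555 = 5.55 mmol/L, which agrees with 100 / 18.016 = 5.55. The conversion is right. The 2.71 cut-off is taken as given.

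**2. Insulin users.** Take glucose 110 mg/dL: 110 × 0.0555 = 6.105 mmol/L.

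- Insulin at the cut-off: 2.71 × 22.5 / 6.105 = 9.99 mcU/mL.

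| Assumed insulin reading (mcU/mL) | HOMA-IR | Above 2.71? |
|---|---|---|
| 8 (own insulin only) | 8 × 6.105 / 22.5 = 2.17 | no |
| 20 (injected insulin detected by the assay) | 20 × 6.105 / 22.5 = 5.43 | yes |
| 3 (own insulin suppressed, injected product not detected) | 3 × 6.105 / 22.5 = 0.81 | no |

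Starting from 8, only 9.99 − 8 = 1.99 mcU/mL of detected injected insulin is enough to change the class. The documents do not say which injected products the assay detects, so the direction of the distortion is open.

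**3. How many patients.** The documents give no share. At an assumed 5–20 %, 28 × 0.05 = 1.4 to 28 × 0.20 = 5.6, or roughly 1 to 6 per group. Zero is also possible.

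**4. Effect on a group mean, illustration only.** One patient moving from 2.17 to 5.43 shifts a 28-patient mean by (5.43 − 2.17) / 28 = 0.12; three such patients shift it by 0.35. The documents give no SD or expected change for HOMA-IR, so these shifts cannot be judged large or small.

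**5. Beta-cell purpose.** Hold HOMA-IR at 2.71, so insulin × glucose = 2.71 × 22.5 = 60.975.

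- Glucose 5.0 mmol/L: insulin 60.975 / 5.0 = 12.2; insulin per unit glucose 2.44.
- Glucose 10.0 mmol/L: insulin 60.975 / 10.0 = 6.1; insulin per unit glucose 0.61.

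The index is identical while insulin per unit glucose differs fourfold (2.44 / 0.61 = 4.0). The formula therefore cannot report secretory capacity. This holds whatever separate beta-cell index one prefers.

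**The case against.** The strongest reply is that the insulin-user point is an omission. The article does not say in terms that every participant is included; it says only that the index follows once glucose and insulin are available. A full protocol or analysis plan could restrict it. That is fair as to wording, and it is why the point is minor. It does not remove the point. The article states the rule, formula and cut-off, admits insulin users, and sets no limit; followed as written, the rule yields uninterpretable values in those patients.

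The second reply concerns weight, and it largely stands. HOMA-IR is not named under the primary or secondary outcome measures, the sample size or the statistics, and no analysis of the 2.71 classification is specified. The Adverse events section counts metabolic changes among laboratory events but does not name HOMA-IR. No beta-cell endpoint or hypothesis appears anywhere, so that clause is an inaccurate statement of purpose and no planned result is lost with it.

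A reader might go further and infer that the metabolic results as a whole are invalid, that the metabolic question rests on HOMA-IR alone, or that a few insulin users would drive the mean change. The documents do not support these readings. LDL-C, the urinary albumin-to-creatinine ratio and estimated GFR are also derived, and glucose, glycated Hb, lipids and uric acid are measured directly. No SD is given against which to judge a shift in the mean. Randomization gives no reason to expect insulin users to gather in one arm, so the likelier effect on a between-group comparison is added noise, not bias.

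**Conclusion.** The point holds as a minor one, confined to one index within the metabolic research question. In any enrolled participant who uses exogenous insulin, HOMA-IR and its classification at 2.71 are not interpretable, and the protocol does not set those participants apart. The claim that HOMA-IR determines beta-cell function is contradicted by the only formula given. The beta-cell part is certain from the text and, taken alone, close to editorial. The insulin-user part rests on reading unrestricted wording as applying to all, and its size depends on a share of insulin users that is not given and may be nil. Blood pressure and arterial stiffness conclusions, and the sample size, are unaffected.

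**What to change.** In General biochemistry assessment, state that HOMA-IR and the 2.71 classification are computed and analysed only in participants not using exogenous insulin at either sampling time, and that fasting glucose and glycated Hb are reported for insulin users. Report the number left out in each arm.

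In the same section, either delete the beta-cell purpose or define a separate beta-cell index, with its formula written out, from the same fasting samples and also in non-users only. Deletion is simpler, because no objective or outcome calls for a beta-cell measure.

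The cost is a change of wording and perhaps a few fewer patients in this one index. Eligibility, samples, visits and sample size do not change.
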